#### Clinicians

Potential participating clinicians must be employed by the PFCC at the Peter MacCallum Cancer Centre or the Royal Melbourne Hospital and involved in providing genetic counselling and testing to patients. Potential participating clinicians include associate and certified genetic counsellors, clinical geneticists, clinical genetic fellows, medical oncologists, and gastroenterologists.

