## Data analysis

### Sample size

A total sample size of 246 participants, 123 per group, is required for 90% power to demonstrate that GPRI superior to usual care with a two-sided 5% significance level. This sample size is based on the following assumptions: a clinically meaningful absolute treatment difference in mean change in GCOS-24 scores from baseline to 2 weeks after the second PFCC appointment of 10 units in favour of GPRI (increase) [25], standard deviation (SD) of 20 units equal in each group, and at each time point (baseline, 2 weeks after first PFCC appointment, and 2 weeks after second PFCC appointment) [25], and conservatively no correlation between baseline and repeated measures of GCOS-24 scores. Attrition is estimated to be similar to another genetic counselling intervention study where approximately 30% participant attrition was observed [31].

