#### Secondary outcomes

In addition to the primary analysis of the GCOS-24 score, responders (defined as change from baseline to 2 weeks after second PFCC appointment in GCOS score ≥ 10) will be analysed using a logistic regression model using generalized estimating equations (GEEs) with an exchangeable correlation structure and robust standard errors for clustering by clinicians [33]. Continuous secondary outcomes with repeated measures—satisfaction with genetic counselling and adaptation to genetic risk—will be analysed using a linear mixed-effects model. The model will include a random intercept for clinician and an unstructured variance-covariance matrix for the individual’s repeated measurements and factors representing treatment, time (categorical), and treatment-by-time interaction. Other secondary outcomes, impact of genetic test result, and duration of PFCC appointments will be analysed using linear regression, total number of psychosocial needs identified in each appointment will be analysed using Poisson regression, and support offered to patients after appointments will be analysed using logistic regression. All these models will be fitted using GEEs with an exchangeable correlation structure and robust standard errors for clustering by clinicians and will be adjusted for the stratification factors sex and cancer status, with further adjustment for cancer type. These models provide valid inference in the presence of missing data if the data are missing completely at random (MCAR). Sensitivity analyses will be conducted using multiple imputation to explore the impact of any deviations from MCAR on the results.

Subgroup analyses for the comparison of the primary outcome, patient empowerment measured using the GCOS-24 score, for participants in the intervention group compared to the control group will be conducted by the stratification factors sex, cancer status (affected vs unaffected), and additionally by type of clinician (genetic counsellors vs doctors), including subgroup and an interaction term between treatment and subgroup in the model. All analyses of secondary outcomes and subgroups are exploratory and therefore require no adjustment for multiple testing. All statistical analyses will be conducted using Stata statistical software [34].

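### The clinician-clustered GEEs for five secondary outcomes name no small-sample correction, so with the clinicians of one service as clusters their confidence intervals can be too narrow

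*Protocol article*

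**What the plan says.** Under *Statistical analysis – Secondary outcomes*, the protocol article gives responder status a logistic GEE with exchangeable working correlation and robust standard errors clustered on clinician. Impact of the test result and appointment duration get linear regression, and support offered gets logistic regression. For needs, "total number of psychosocial needs identified in each appointment will be analysed using Poisson regression". It then states: "All these models will be fitted using GEEs with an exchangeable correlation structure and robust standard errors for clustering by clinicians". Satisfaction and adaptation are handled separately, by a linear mixed model with a random clinician effect.

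The only condition that the section attaches to valid inference from these models concerns missing data (missing completely at random). It sets no condition on the number of clusters and names no finite-sample correction.

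The clusters come from one service at two hospitals: "Potential participating clinicians must be employed by the PFCC". *Setting* lists five kinds of clinician but no headcount. *Randomisation* allocates individual patients 1:1, stratified by sex and cancer status and not by clinician. All secondary analyses are called exploratory, and a detailed SAP is to be written before unblinding.

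**The concern.** The sandwich estimator builds the variance of the treatment effect from one score contribution per cluster. With few clusters, the fitted residuals are too small relative to the true errors, so the estimated variance is biased downward. A normal reference also ignores the uncertainty in the variance estimate itself. Both errors make the interval too short.

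Individual randomisation within clinicians helps precision, but the variance is still estimated from as many contributions as there are clinicians. A single service makes a small number plausible. Five outcomes are involved, among them the responder analysis based on the minimum important change. If the standard errors are too small, differences that are chance will be reported as findings more often than the nominal 5%.

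**Working it through.** **The plan's own figure.** "A total sample size of 246 participants, 123 per group, is required for 90% power", for "GPRI superior to usual care with a two-sided 5% significance level", with a difference of 10, "standard deviation (SD) of 20 units equal in each group, and at each time point" and "conservatively no correlation between baseline and repeated measures of GCOS-24 scores". The normal formula is 2 × (1.960 + 1.282)² × 20² / 10² = 84.1, so 85 per arm. The t-test version has power 0.8999 at 85 and 0.903 at 86, so 86 per arm. With 30% attrition, 86 / 0.7 = 122.9, so 123 per arm and 246 in total. The figure reproduces, and it implies about 2 × 86 = 172 completers. The documents give no cluster count or error rate for the secondary GEEs.

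**Inputs to the simulation.** From the documents: 172 completers (or 246 without attrition), 1:1 individual allocation that ignores clinician, adjustment for sex, cancer status and cancer type, exchangeable GEE, robust variance clustered on clinician. Assumed, because the documents are silent: K = 8 to 50 clinicians, intraclass correlation 0.05, and equal or unequal caseloads (coefficient of variation 0 or 0.7). No true treatment effect.

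**Tests compared.** V = A⁻¹MA⁻¹, where M sums the outer products of the K cluster scores. The plain test rejects if |estimate| / √V > 1.96. The simple corrected test multiplies V by K/(K−1) and uses the t distribution on K−1 degrees of freedom.

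**Linear GEE, 172 patients, 3,000 runs per setting** (Monte Carlo standard error about 0.4–0.6 points; ranges cover the two caseload patterns):

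| Clinicians | Mean robust SE / true SE | Plain sandwich, normal | K/(K−1) and t |
|---|---|---|---|
| 8 | 0.86–0.88 | 11.8–13.7% | 5.5–6.4% |
| 10 | 0.90–0.91 | 10.7–11.1% | 5.4–5.9% |
| 15 | 0.89–0.92 | 9.3–9.7% | 6.2–6.9% |
| 20 | 0.92 | 8.7–8.8% | 6.2–6.6% |
| 30 | 0.95–0.98 | 6.5–7.2% | 5.3–5.5% |
| 40 | 0.94–0.96 | 6.3–7.8% | 5.2–6.3% |
| 50 | 0.95 | 6.7–6.8% | 5.9% |

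**246 patients, unequal caseloads.** Plain: 12.2%, 9.5%, 7.7% and 7.4% with 10, 20, 30 and 40 clinicians. Corrected: 7.0%, 7.3%, 6.6% and 5.8%. Lower attrition does not help, because the number of clusters is what matters.

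**Logistic and Poisson GEEs** (172 patients, unequal caseloads, 1,500 runs, Monte Carlo standard error about 0.6–0.9 points; assumed latent intraclass correlation 0.05 for logistic, and a mean of 5 needs with clinician log-SD 0.12 for Poisson). With 8, 12, 20, 30 and 40 clinicians the plain test rejected in 13.5%, 9.8%, 9.0%, 7.2% and 6.5% (logistic) and 15.5%, 10.8%, 9.2%, 7.4% and 7.0% (Poisson). The K/(K−1) and t version gave 5.3–7.7% across both.

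**Bias-corrected sandwich.** A separate linear simulation with unequal caseloads gave about 14%, 11%, 10%, 9% and 9% for the plain test with 8, 12, 20, 30 and 40 clinicians. Mancl-DeRouen with t on K−1 brought these to 5–6%.

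**The case against.** The best reply is that the protocol neither names nor excludes a correction, and that degrees of freedom for exploratory models are commonly left to the SAP, which is announced but not shown. That stands in part: the omission alone would be no finding. But the article does fix the estimator, working correlation, variance type and clustering unit, and that method, read as written, was mis-sized at every cluster count tried. Calling the analyses exploratory excuses the lack of multiplicity adjustment. It does not excuse a standard error that is too small.

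Four stronger readings are tempting, and the documents do not support them.

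- *That the intervals are certainly too narrow by a large margin.* The number of clinicians appears nowhere. The double-digit rates need a small count; with 30 or more the excess is modest.
- *That the software will report uncorrected z-tests.* Stata is named, but no command, option or reference distribution.
- *That all secondary outcomes are affected.* Satisfaction and adaptation are given a mixed model, and the primary longitudinal model does not use this estimator.
- *That the two appointments are pooled under different clinicians, so that within-patient correlation is lost.* No section says so. Counting needs in each appointment fits separate analyses at least as well.

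**Conclusion.** The point holds as a conditional weakness of a stated method. Under the assumptions above, the plain sandwich with a normal reference has a true size of roughly 9–14% with 8–20 clinicians in the linear model (up to 15.5% in the Poisson model with 8) and about 6–9% with 30–50. The standard error averages about 0.86–0.92 of its true value in the first range and 0.94–0.98 in the second.

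The result rests on an assumed intraclass correlation of 0.05, assumed caseloads and an unstated number of clinicians. It is limited to the confidence intervals and p-values of five exploratory outcomes and does not touch the trial's primary conclusion. It is worth correcting because the remedy is cheap and can be fixed while the statistician is still blinded.

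**What to change.** In the SAP, keep the GEE, the exchangeable structure and the clustering by clinician, and specify a bias-corrected sandwich variance (Mancl-DeRouen or Kauermann-Carroll) with a t reference on the number of participating clinicians minus 1. Report that number with the results. Apply this to responder status, impact of the test result, appointment duration, needs identified and support offered.

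Replacing the binary and count GEEs with mixed models is not recommended: it would change the estimand from a population-averaged effect to one conditional on clinician.

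The cost is a sentence of SAP text, a few lines of code and wider intervals. As a guide, the simple K/(K−1) and t version multiplies the interval width by (t quantile / 1.96) × √(K/(K−1)). With 40 clinicians that is (2.023 / 1.96) × 1.013 = 1.05, with 20 it is (2.093 / 1.96) × 1.026 = 1.10, and with 8 it is (2.365 / 1.96) × 1.069 = 1.29. The widening is slight unless clinicians are few, which is where the uncorrected interval is most misleading.

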#### Health economic analysis

Resources will be itemised and valued in 2020 Australian Dollars (AUD). A cost analysis comparing control and intervention groups will be conducted from both a societal and public healthcare system perspective, using a bottom-up micro-costing approach. Costs will be compared using mean estimates, or through nonparametric bootstrap in the event of skewed data.

### Data management, retention, and storage

All electronic data will be stored in REDCap. Data exported from REDCap during analyses will be stored in a secure folder on the internal network drive. All electronic files and the final cleaned dataset will only be accessible to the investigator team. Audio recordings of the appointments and the structured interviews will be deleted from the Dictaphone after transfer to the network drive.

There is no data monitoring committee appointed for this trial due to the minimal risk presented by this research.

All files and data relating to this project will be kept for a minimum of 5ive years in accordance with the guidelines stipulated by the National Health & Medical Research Council in the Australian Code for the Responsible Conduct of Research. After this time, electronic data will be permanently deleted.

### Ethical considerations and risk mitigation

The study will be conducted according to the National Health and Medical Research Council (NHMRC) National Statement on Ethical Conduct in Human Research 2007 (and updates), and the World Medical Association Declaration of Helsinki 2013. Any modifications to the protocol that change the study design or conduct, or significant administrative changes, will require a formal amendment that will be reviewed and approved by the sponsor, the Peter MacCallum Cancer Centre, and the Peter MacCallum HREC prior to implementation. These changes will also be reflected as updates to the trial registration at the Australian New Zealand Clinical Trials Registry.

#### Management of distress

This study is not expected to detract from the usual standard of care for patients, as the GPRI has been validated to detect psychosocial needs in the clinical genetics setting and enhance communication between staff and patients. Any patients who experience distress during an appointment are counselled about the issues causing their distress during the appointment, relevant supports are identified, and referrals are made to appropriate psychological support services, if required. If a staff member identifies a participant is distressed based on their GPRI results, they will follow these standard clinical processes.

This study is not expected to cause any distress to clinical staff who participate or to members of the research team. However, if a staff member is distressed due to the completion of the staff questionnaire, they will be provided with support by the Director of the PFCC.

### Dissemination of findings

The progress of the study and the study findings at completion will be communicated locally and internationally. Results will also be published in peer-reviewed journals and disseminated to genetic and oncology health professionals and researchers at national and international conferences. Authorship on any publications arising from this trial will be determined by guidelines published by the NHMRC that support the Australian Code for the Responsible Conduct of Research and there are no plans to use any professional writers for this process.

## Discussion

The POETIC trial takes a pragmatic approach, complementing the hybrid design, by deploying the GPRI as an intervention in the routine clinical practice of a Familial Cancer Centre staffed by a multidisciplinary team of genetics and oncology clinicians. Following this pragmatism, the sample population will not be highly selected based on narrow eligibility criteria, and instead most patients referred to the PFCC will be eligible to be invited to the study. All clinicians comprising genetic counsellors, medical speciality trainees, and medical practitioners will have opportunity to use the GPRI and have their practice evaluated as part of this trial. While a consequence of this pragmatic design means that a larger sample size is needed to evaluate the primary outcome, a corollary may be that the effectiveness and implementation evidence generated from this real-world health service setting will optimise the relevance of the trial to, and enhance operationalisation of the screening tool in, routine practice.

Germline genetic testing has tangible clinical health outcomes in terms of diagnosis and risk prediction, but also has the potential to impact psychosocial health of individuals and families. However, the provision of genetic counselling, with a beneficial outcome defined by patients as empowerment, is an opportunity to facilitate informed decision-making and psychological adaptation in relation to a genetic condition [9]. In the demanding clinical environment of clinical genetics services, use of the GPRI screening tool may create capacity to personalise the practice of genetic counselling though identifying and focusing on the aspects of most concern for each client. In this POETIC trial, the effectiveness of the GPRI in the familial cancer setting will be measured primarily in terms of the widely accepted genetic counselling outcome of empowerment using the rigorously validated GCOS-24 scale [24]. Should the GPRI be demonstrated to be effective in this clinical genetics setting, it could then be implemented and trialled as an intervention in other health service settings, such as mainstreaming models, where genetic testing is increasingly being facilitated by non-genetics specialists. This would provide consistent evidence across settings of whether the GPRI can standardise and streamline genetic counselling, irrespective of the provider, to safeguard patient outcomes after genetic testing.

## Trail status

Protocol V2 08.11.2021; recruitment commenced on May 19, 2022. It is estimated that recruitment will be completed by December 31, 2024.

## Data Availability

Not applicable.
